**Extended Trial**

The investigators and sponsor decided to start the extended trial from the 2.0 mg/kg dose group at a meeting on Oct. 18, 2016. Pharmacokinetic data from Q2W administration are collected repeatedly. The dose next to 2.0 mg/kg is determined by the investigators. Q2W dosing means 1 treatment cycle includes 2 doses. The efficacy evaluation is performed once every 2 treatment cycles.

On July 4, 2017, the investigators and sponsor decided to let 3-5 study sites participate in the extended trial phase based on the current study results. At least 10 patients with HER2 ICH 2+/FISH- and at least 20 patients with HER ICH 2+/FISH+ or ICH 3+ with advanced solid tumors (gastric cancer is preferable) are enrolled and administered at 2.0 mg/kg Q2W until disease progression or intolerable adverse reactions.

# 4 Criteria for Subject Selection

## 4.1 Inclusion Criteria

1. Have signed informed consent forms voluntarily;

2. 18-75 years old;

3. Having an ECOG performance status score of 0 or 1;

4. With an expected survival of more than 12 weeks;

5. Diagnosed histologically or cytologically with local advanced or metastatic HER2-positive malignant solid cancer, and under one of following situations: standard treatment-refractory (disease progression or no response), treatment-resistant, unable to receive treatment, or the standard treatment is unavailable;

6. "HER2-positive" refers to IHC 2+ or 3+ (subjects should go through an FISH assay in extended trial phase, and obtain an HER2 expression of IHC 2+/FISH-, IHC 2+/FISH+, or IHC 3+);

7. Having measurable or evaluable lesions according to RECIST 1.1;

8. Having sufficient bone marrow, liver and kidney functions (based on the normal value of the clinical trial site):

Absolute neutrophil count (ANC) ≥ 1.5×109/L,

Platelets ≥ 100×109/L,

Total serum bilirubin ≤ 1.5×upper limit of normal (ULN),

Without liver metastases, ALT, AST or ALP ≤ 2.5×ULN; with liver metastases, ALT, AST or ALP ≤ 5×ULN, with normal serum creatinine levels and INR ≤ 1.5×ULN, APTT ≤ 1.5×ULN;

9. Male or female patients of childbearing potential must agree to use effective methods of contraception (such as double-barrier contraceptive methods, condoms, oral or injectable contraceptives and intrauterine devices) during the study period and within 30 days after the last dosing;

10. Echocardiographic LVEF (left ventricular ejection fraction) ≥ 50%.

## 4.2 Exclusion Criteria

If any one of the following conditions is met, the patients must be excluded from this study:

1. Pregnant (positive pregnancy test prior to dosing) or breast-feeding women;

2. Patients with active Hepatitis B and/or Hepatitis C;

3. Patients who underwent major surgeries within 4 weeks prior to dosing and not fully recovered;

4. Patients who underwent palliative radiotherapy for bone metastasis within 2 weeks before the initiation of the trial;

5. The toxicity of previous anti-cancer therapy has not returned to 0 or 1 level as specified in CTCAE v4.0 (except for hair loss);

6. Patients who received anti-cancer treatment with any other clinical trial drug within 28 days before the first dosing;

7. Patients with clinically significant active infection based on the investigator's judgment;

8. Patients with a history of immunodeficiency, including those are HIV-positive, or patients with other acquired or congenital immune deficiency, or a history of organ transplantation;

9. Patients with serious complications such as gastrointestinal bleeding, intestinal obstruction, intestinal paralysis, interstitial pneumonia, pulmonary fibrosis, renal failure, glaucoma and uncontrolled diabetes;

10. Patients with a history of acute myocardial infarction, unstable angina pectoris, stroke or transient ischemic attack within 6 months prior to the enrollment, or with NYHA Class 2 or higher congestive heart failure;

11. Patient who has been determined to have insufficient adherence to this clinical study;

12. Patients who has undergone chemotherapy or HER2 targeted therapy within 21 days before the first administration;

13. Patients who underwent long-term treatment with systemic steroids (note: short-term users may be enrolled 2 weeks after drug withdrawal);

14. Patients with uncontrolled primary or metastatic brain tumors;

15. Patients with Grade 2 or higher peripheral neuropathies;

16. Patients with a history of uncontrollable mental illness.

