# 7. Outcome Measures

(1) Demographic data: Age, sex, height, and body weight.

(2) Vital signs: Respiration, sitting blood pressure, sitting pulse, and body temperature.

(3) Physical examination: Nervous system, mental system, respiratory system, cardiovascular system, gastroenteric system, and skin. ECOG evaluation;

(4) Laboratory test

Table 4 lists items of laboratory test to be performed during the study. For specific test time points, please see Appendix 2 Trial Flow Chart.

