## 8.1 Screening Period

Unless otherwise specified, the following steps have to be completed in 28 days before starting the treatment with the study drug:

- Case history and demographic data acquisition, and recording (by the investigators) identity card, correspondence address, and phone number of every patient, though such information will not be recorded in a CRF;
- Detailed inquiry of case history, and detailed comprehensive physical examination: ECOG score, height, body weight, vital signs, and checkup of various organs;
- Routine blood test, and routine urinalysis;
- Blood chemistry (myocardial zymogram, cardiac troponin, GGT, ALT, AST, ALP, TP, ALB, ALB/GLO, TBIL, IBIL, DBIL, BUN, Cr, Glu, K^+^, Na^+^, Cl^－^, LDH, TC, TG, HDL-C, and LDL-C);
- Blood coagulation tests (INR, APTT, and PT);
- HER2 protein expression and gene amplification assays: immunohistochemistry (ICH), and fluorescence in situ hybridization (FISH);
- Tumor markers (specific test items will be determined by the investigators depending on the tumor type);
- Virology test (HIV, five HBV tests, and HCV);
- Electrocardiographic examination for 3 times at intervals of 5 minutes, particularly observing QT, QTc and P-R intervals (within 7 days before the initiation of the trial);
- Echocardiographic examination to observe LVEF (within 28 days before the initiation of the trial);
- CT or MRI scans of the chest, abdomen, pelvis, brain and other relevant lesions (within 28 days before the initiation of the trial);
- Urine HCG tests for female patients of childbearing age to exclude pregnant subjects;
- Assessment of current concomitant medications and treatments;
- Assessment of current symptoms.

Written informed consent forms must be obtained before any of the study-related medical procedures. CT/MRI scan results obtained prior to the signing of informed consent forms can be used for the tumor assessments during screening (examination must be made within 28 days before the initiation of the trial).

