## 8.5 Conclusion/Withdrawal

At the end of the treatment or in case of withdrawal, the following items should be tested if the patient has not undergone the examinations within 21 days before the study ends:

- Comprehensive physical examination: ECOG performance status, body weight and vital signs;
- Routine blood test, and routine urinalysis;
- Liver function, renal function, blood glucose, blood lipids and blood electrolytes;
- Urine HCG of female subjects of childbearing age;
- 12-lead electrocardiogram, echocardiogram;
- CT or MRI scans of the chest, abdomen, pelvis, brain and other relevant lesions (if has not been assessed within the preceding 3 weeks);
- Assessment of adverse events;
- Assessment of concomitant medications/treatments.

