# Appendix 2. Trial Flow Chart of Dose Escalation Phase - Q2W Administration

| Visit Time Points | Screening | Cycle 1-2 | | Extended Trial | Conclusion/Withdrawal |
| --- | --- | --- | --- | --- | --- |
|  | -28 | D 1 (±1) of Cycle 1 | D 1 (±1) of Cycle 2 | D 1 (±2) of Cycle 3-n |  |
| Informed Consent | √ |  |  |  |  |
| **General Medical History Collection** |  |  |  |  |  |
| Inclusion/Exclusion Review | √ |  |  |  |  |
| Filling of General Information | √ |  |  |  |  |
| Past medical history | √ |  |  |  |  |
| Combined diseases and treatment history | √ |  |  |  |  |
| **ECOG** Scale | √ | √ |  |  |  |
| Virology test | √ |  |  |  |  |
| **Safety Examination** |  |  |  |  |  |
| Vital signs | √ | √ | √ | √ | √ |
| Routine blood test | √ | **√△** | **√** | √ | √ |
| Routine Urinalysis | √ | **√△** | **√** | √ | √ |
| Blood chemistry | √ | **√△** | **√** | √ | √ |
| Blood coagulation test | √ | **√△** | **√** |  |  |
| Pharmacokinetics and Immunogenicity |  | See Item 6 in the Clinical Trial Protocol | |  |  |
| Electrocardiography | √ | √※ | √※ | √☆ | √ |
| Urine pregnancy test | √ |  |  |  | √ |
| Echocardiography | √ | √★ | | | √ |
| HER2 Detection | √ |  | | |  |
| Tumor Marker ▲ | √ | **√△** |  | √ |  |
| Imaging Examination# | √ | Once every 2 cycles | | |  |
| Efficacy Evaluation |  | Once every 2 cycles | | |  |
| Record the adverse events |  | √ | √ | √ | √ |
| Record concomitant medication | √ | √ | √ | √ | √ |

△ If the interval between the 1st dose and the screening period should be no more than 7 days, no reexamination is required.

※ Perform ECG examination 3 times at intervals of 5 minutes before each dose. Monitor ECG during medication. Perform ECG examination 3 times at intervals of 5 minutes within 1-2 hours after administration.

★ If the subject experiences precordial chest pain, palpitations or other symptoms, or has an abnormal ECG, CK-MB test and echocardiography may be added.

▲ Specific test items will be determined by the investigators depending on the tumor type.

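### The scheduled pregnancy test behind exclusion 1 may be up to 28 days old at first dose, because no flow chart repeats it at Cycle 1 Day 1

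*Protocol*

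**What the plan says.** Exclusion 1 (Protocol Section 4.2) removes "Pregnant (positive pregnancy test prior to dosing) or breast-feeding women". It sets no interval between the test and the first dose.

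Section 8.1 gives the general screening rule: "Unless otherwise specified, the following steps have to be completed in 28 days before starting the treatment with the study drug". The pregnancy line in that list reads "Urine HCG tests for female patients of childbearing age to exclude pregnant subjects" and has no window of its own. The ECG line in the same list does have one, of 7 days.

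Section 7 introduces the laboratory items in Table 4 and then sends the reader elsewhere for timing: "For specific test time points, please see Appendix 2 Trial Flow Chart". In Appendices 2, 3, 4 and 5 the row "Urine pregnancy test" is ticked at screening and at Conclusion/Withdrawal, and nowhere else. The exit test is confirmed in Section 8.5 ("Urine HCG of female subjects of childbearing age").

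In the same charts, some Cycle 1 Day 1 cells carry √△, explained by the footnote "If the interval between the 1st dose and the screening period should be no more than 7 days, no reexamination is required". The pregnancy row does not carry that mark. Section 8.2 requires urinalysis before each administration and does not name HCG.

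Inclusion 9 (Section 4.1) says that patients of childbearing potential "must agree to use effective methods of contraception" during the study and for 30 days after the last dose.

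**The concern.** Exclusion 1 exists to keep a pregnant woman from her first exposure to the drug. Section 1.1 describes the payload, MMAE, as a cytotoxic microtubule inhibitor. The schedule lets that criterion be recorded as met on a test done up to four weeks earlier. In that interval a pregnancy could begin through contraceptive failure or non-adherence, or one that was too early to detect at screening could become detectable. Neither would be picked up, because nothing scheduled between screening and the first dose looks for it.

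What is at stake is patient and fetal safety, and how well exclusion 1 does its job. No analysis set, DLT count, response rate or PK parameter depends on it.

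**Working it through.** The protocol states no figure for the allowed age of the pregnancy test at first dose, so there is none to reproduce. The check compares the places that set the timing.

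**Inputs**
- Default screening window, Section 8.1: 28 days. The HCG line has no shorter window.
- △ limit, footnote to each of Appendices 2 to 5: 7 days.
- Exit rule, Section 8.5: items including HCG are tested if not done within the 21 days before the study ends.

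**Step 1. Does any chart repeat the HCG at Cycle 1 Day 1?**

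| Chart | Screening | Cycle 1 Day 1 | Conclusion/Withdrawal |
| --- | --- | --- | --- |
| Appendix 2, Q2W escalation | ticked | blank | ticked |
| Appendix 3, Q3W escalation | ticked | blank | ticked |
| Appendix 4, Q2W extended trial | ticked | blank | ticked |
| Appendix 5, QW escalation | ticked | blank | ticked |

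Charts with a pregnancy test at Cycle 1 Day 1: 0 of 4. Q3W escalation was stopped on July 4, 2017, so 4 − 1 = 3 of these charts serve regimens that continued or opened after that date.

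**Step 2. How old may the test be?**
The maximum age at first dose is the longest window allowed for the item, which is 28 days.

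**Step 3. How does that compare with other items at the same visit?**
In each chart five rows carry √△ at Cycle 1 Day 1: routine blood, urinalysis, chemistry, coagulation and tumor marker. Their maximum age is 7 days. The HCG may be up to 28 − 7 = 21 days older.

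**Step 4. How does it compare with the protocol's rule for HCG at exit?**
At exit, an HCG more than 21 days old must be repeated. Before the first dose, one of 22 to 28 days is accepted, so the entry rule is looser than the exit rule by 28 − 21 = 7 days.

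**Step 5. Does Table 4 close the gap?**
Table 4 (Section 7) puts routine urinalysis and the pregnancy test under one item name, and urinalysis is required before each administration. A site could read the pre-dose urinalysis as including HCG. However, Section 7 hands the timing of Table 4 items to the flow chart. The charts list urinalysis and pregnancy test as separate rows, with √△ on the first and a blank on the second, and Section 8.2 names urinalysis alone. The more natural reading is that HCG is not repeated.

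**After the fix.** Under a 7-day limit the maximum age falls from 28 to 7 days.

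**The case against.** The strongest case against is that nothing here is an error. A reader might infer that exclusion 1 and the schedule contradict each other. They do not: a test 28 days before the first dose is still a test before dosing. A reader might also infer that the protocol breaks its own 7-day standard. It sets no such standard for pregnancy tests; the 7 days belong to the △-marked rows and to the screening ECG. Virology and echocardiography, which also bear on eligibility, rest on the same 28-day window. These points stand, and they keep this a question of how well the schedule is set.

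Inclusion 9 also covers part of the interval, any positive test before dosing would exclude the patient, and nothing stops a site from repeating the test. That too stands, in part. Agreement to contraception does not detect its failure, and the protocol asks for HCG in addition to contraception, so it does not treat agreement as enough.

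Table 4 gives some sites a reason to test with the pre-dose urinalysis. That reading is possible but less natural, and the fact that sites could differ is itself a reason to settle the timing.

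Finally, a 7-day limit does not catch every very early pregnancy, and it leaves later doses without a scheduled HCG. Both are true. Exclusion 1 governs entry, so the point is confined to the first dose, and the fix narrows the gap without closing it.

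**Conclusion.** The point holds as a weak safety schedule. A site following Section 8.1 and the flow charts may give the first dose on an HCG up to 28 days old, up to 21 days older than the △-marked results, and that test may no longer reflect pregnancy status.

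This rests on reading the flow charts as governing timing, as Section 7 says, and on treating urinalysis and pregnancy test as separate items, as the charts do.

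The 28 days is an outer limit and not an expected gap. The protocol gives neither the usual interval from screening to first dose nor the number of women of childbearing potential, so no count of affected patients can be derived. A reader might go further and infer that pregnant women would be dosed, or that the screening result is wrong by Cycle 1; the document supports neither. No estimate, DLT decision or analysis changes. This is a cheap improvement worth considering.

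**What to change.** Make one of two changes, which have the same effect:

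- In Section 8.1, give the urine HCG line a window of 7 days before the first dose.
- Or put √△ in the pregnancy row at Cycle 1 Day 1 in Appendices 2, 4 and 5, and in Appendix 3 for consistency only, since Q3W escalation was stopped.

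The edit is one phrase or one mark per chart. In use, the cost is at most one repeat urine HCG for each woman of childbearing potential screened more than 7 days before her first dose. The △ rule already calls for a repeat urinalysis from such a patient at that visit, so no extra collection should be needed.

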## 4.3 Withdrawal Criteria

Subjects can withdraw from the study at any time without any reason. Subjects must withdraw from the study when the any of the following conditions occur:

Investigators consider it necessary to stop the trial from the perspective of medical ethics;

Subjects are not suitable to continue with the trial due to severe adverse event(s);

Subjects are poorly compliant and no longer receiving medications or testing before completing all the trials, or receive other anti-cancer therapies before completion of the trials and fail to adhere to the planned completion of trials;

Subjects ask for withdrawal from the trial and withdraw their informed consent forms.

## 4.4 Criteria for Termination of Trial

Termination of a trial means that all trials have been discontinued prior to the scheduled completion specified in the protocol. Termination of the trial is mainly to protect the rights of subjects, to ensure the quality of the trial and to avoid unnecessary economic losses. Early termination of clinical trials should be promptly notified to all parties involved in the study.

Major errors are found during the trial so that it is difficult to evaluate the safety of the drug;

The sponsor requires to terminate the trial (e.g, for reasons of funding and management, etc.);

The CFDA or the Ethics Committee order the termination of the trial for some reason.

# 5. Investigational Drug

(1) Test Product: omitted

(2) Intended Route and Method of Clinical Administration: Intravenous infusion, not to be given by intravenous push or bolus. Measure 60 mg of this product and dissolve with 6.0 mL of sterile water for injection. After dissolution, dilute with 5% glucose injection to about 250 mL for intravenous infusion. The diluted RC48-ADC infusion solution should be used immediately. Otherwise, the solution can be stored in a refrigerator at 2 °C to 8 °C for 24 h. Do not shake.

Administer by intravenous drip for at least 30 min.

Patient should be observed during the first infusion and at least 90 minutes after start of the administration for fever or chills.

Subsequent infusion: If the previous infusions are well tolerated, the patient should be observed during the infusion and at least 30 minutes after the infusion.

Physical signs and symptoms should be monitored during and after infusion. If serious infusion-related reactions or hypersensitivity reactions occur, slow down or suspend the infusion and give appropriate medical treatment. Terminate permenantly in the event of life-threatening reactions to infusion.

For detailed drug formulation, refer to the "Operation Manual of RC48-ADC Investigational Drug Formulation".

RC48-ADC local irritation tests showed that in cynomolgus monkeys and SD rats each given repeated intravenous infusions Q2W at respective concentrations of 0.6-2.4 mg/mL and 1.2-4.8 mg/mL, no irritation was seen in response to drug administration. In vitro hemolysis testing found that RC48-ADC at 1.8 mg/mL did not exhibit hemolytic or agglutinating effects. It can be concluded that a concentration of infused RC48-ADC for human should be safely tolerated within 1.8 mg/mL.

(3) Specification: 60 mg/piece;

(4) Shelf life: 18 months before retest;

(5) Storage condition: 2-8 °C refrigerated storage and transportation;

(6) Administration: Intravenous infusion.

The initial dose of this study is determined 0.1 mg/kg and the maximum dose is 4.0 mg/kg. A total of 9 groups are required. According to animal experimental results, the possible MTD of this product is predicted to be between 2-3.5 mg/kg. The number of cases in each group is shown in Table 1.

**Table 1. Dosage escalation grouping.**

| **Dose** | **Number of cases** |
| --- | --- |
| 0.1 mg/kg | 1 |
| 0.5 mg/kg | 1 |
| 1.0 mg/kg | 3-6 |
| 1.5 mg/kg | 3-6 |
| 2.0 mg/kg | 3-6 |
| 2.5 mg/kg | 3-6 |
| 3.0 mg/kg | 3-6 |
| 3.5 mg/kg | 3-6 |
| 4.0 mg/kg | 3-6 |

Subjects are enrolled in the traditional 3+3 mode from 1.0 mg/kg dose group forward.

If a dose has passed the safety observations in another Phase I clinical trial (at the Cancer Hospital, Chinese Academy of Medical Sciences), investigators and sponsors may adjust the dose increment in dose escalation trial, or skip this dose and proceed directly to the next dose according to the corresponding results, in order to reduce the patient's exposure to ineffective doses.

During the trial, investigators can adjust the dose increment and maximum dosage based on the results of the trial.

On Oct. 18, 2016, investigators and sponsors met and determined an additional dose escalation study for Q3W administration. Starting from the 2.0 mg/kg dose group, 2-3 patients are enrolled. Pharmacokinetic data from Q3W administration are collected repeatedly. The dose next to 2.0 mg/kg is determined based on the results of the dose escalation study with Q2W administration.

2) The original dose-escalation study starting with 2.0 mg/kg Q3W was discontinued. Instead, dose escalation trial is carried out with an initial dose of 1.25 mg/kg, followed by 1.5 mg/kg, in the traditional 3+3 mode with QW administration. Symptomatic supportive treatment is allowed in the DLT evaluation period until MTD is reached. If the 1.5 mg/kg dose group does not reach MTD, the sponsor and investigators will jointly decide on the next escalating doses or whether to terminate the dose escalation trial.

**Extended Trial**

The investigators and sponsor decided to start the extended trial from the 2.0 mg/kg dose group at a meeting on Oct. 18, 2016. Pharmacokinetic data from Q2W administration are collected repeatedly. The dose next to 2.0 mg/kg is determined by the investigators. Q2W dosing means 1 treatment cycle includes 2 doses. The efficacy evaluation is performed once every 2 treatment cycles.

On July 4, 2017, the investigators and sponsor decided to let 3-5 study sites participate in the extended trial phase based on the current study results. At least 10 patients with HER2 ICH 2+/FISH- and at least 20 patients with HER ICH 2+/FISH+ or ICH 3+ with advanced solid tumors (gastric cancer is preferable) are enrolled and administered at 2.0 mg/kg Q2W until disease progression or intolerable adverse reactions.

**Basis for Dosage Interval**

According to the findings of in vitro anti-tumor tests with RC48-ADC, RC48-ADC can inhibit the proliferation of cells with high-expression of HER2. After incubation with breast cancer BT-474 cells (highly expressing HER2) for 1 hour, RC48-ADC (1 μg/mL) and RC48 nude antibody (1 μg/mL) were predominantly localized on the cell membrane. After incubation for 24 hours, they had for the most part entered the cells and were mostly consistent with lysosomes in locations. RC48-ADC and RC48 nude antibodies are known to have similar action characteristics. Therefore, RC48-ADC was predicted to be effective at least 24 h after entering the body.

Mean T1/2 of rat serum ADC after a single intravenous administration of RC48-ADC (4, 8, 16 mg/kg) and SGN-35 (0.5, 5 mg/kg) were 4.9-7.5 days (2.7-62.7 d) and 8.5-14.6 d respectively. There was no dosage-related difference in the half-life and clearance rate within the experimental range, and the exposure was found to increase with the dosage. As different study and measurement methods were applied, it was established that there was no difference in the overview.

The animal trials also showed that RC48-ADC was able to significantly inhibit the phosphorylation of AKT in BT-474/T721 tumor tissues. 4~24 h after RC48-ADC administration, all dosages (1.5 mg/kg~5 mg/kg) showed significant inhibitory effects on AKT phosphorylation and lasted up to 168 h (7 days).

In animal trials, RC48-ADC (1.5 mg/kg and 5 mg/kg) was administered by a single intravenous injection to tumor-bearing nude mice. PK studies found that the level of free MMAE in the serum decreased rapidly, while tumor tissues significantly grew and reached a relatively high level at 24 h. Within the range of 1.5-5 mg/kg, free MMAE in tumor tissues peaked within 1-3 days and remained at a relatively high plateau level within 7 days (refer to Figure 2).

Figure 2. Mean concentration-time curves of free MMAE in serum and tumor tissue after a single IV RC48-ADC injection at 1.5 mg/kg and 5.0 mg/kg to Herceptin-resistant breast cancer BT-474/T721 tumor-bearing nude mice (n=3).

The drug concentration in tumor tissues is in ng/g of tumor weight; and the drug concentration in serum is in ng/mL of serum.

